### Sample size calculations

It is expected that the intervention effects on behavioral and biological primary outcomes will be moderate in size (standardized difference ~ 0.32, equivalent to a mean change in objectively-measured PA of 8 minutes per day [SD = 18 min] and a change in body mass index (BMI) units (age-sex difference from population norm data) of 1.9 kg/m^2 ^[SD = 0.25]) [25,46]. Without accounting for school cluster effects, the number of participants needed to detect a standardized difference of 0.32 with 0.8 power for sedentary behavior (SB-I) and physical activity (PA-I) alone and in combination (SB+PA-I), using a significance level of 0.05 with a two-tailed test, assuming a retention rate of 91% (based on the team's previous experience) and 20 participating schools, would be 340 in total (17 per school). With a previously observed school clustering effect of 0.018 (intra-class correlations [ICCs] for sedentary behavior, physical activity and BMI outcomes estimated using data from a previous intervention study)[44], the minimal total number of participants needed is 520, i.e., 26 per school. Hence, we will conservatively recruit 30 participants per school, giving a total sample size of 600 participants.

Moderate mediated effects of the intervention on the behavioral outcomes are expected (here a moderate mediated effect size is defined as standardized regression coefficients α and β of ~ 0.39)[47]. According to a 2007 simulation study by Fritz and MacKinnon [48], to detect a moderate mediated effect size with 0.8 power, using a significance level of 0.05 with a two-tailed test and bias-corrected bootstrap methods, ~ 61 independent observations are needed. If we assume a 9% rate of loss to follow-up, an average school cluster effect of 0.03 for the mediators (ICCs estimated using data from a previous intervention study)[44] and an average of 30 observations per school (see above), the sample size needed to detect a moderate mediated effect size would be 100 (20 per school). Hence, the sample size needed to detect moderate intervention effect sizes with 0.8 power for the primary outcomes (n = 600) will also be sufficient to detect a moderate-sized effect with 0.8 power for the mediating variables.

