### Data analysis

All statistical analyses will be performed using Stata 9.1 for Windows (StataCorp LP) and will adjust for clustering by observations by school (the unit of randomization). All analyses will be conducted using the intention to treat principle. Generalized Estimating Equations (GEE) [84] will be used to fit regression models to describe the effects of the intervention on key outcome variables among children. Separate models will be fitted to determine differences in key outcome variables in the intervention and control groups.

Separate models will be evaluated for each assessment point (mid-intervention; post-intervention; 12 months follow-up), adjusting for baseline levels of the outcome, and, where appropriate, baseline levels of the mediating variables. PA-I and SB-I intervention conditions will be the predictors of primary interest (entered in the form of two indicator variables and their interaction term). Analyses will be performed excluding and including children who were recruited to the study after baseline. For physical activity outcomes, we will compare the PA-I and SB+PA-I versus the SB-I and C groups. For sedentary behavior outcomes, we will compare SB-I and SB+PA-I versus the PA-I and C groups. For health outcomes, we will compare C versus the other three groups and the SB+PA-I versus the single intervention groups. All models will be adjusted for measured confounders. As it has been argued that adjustment for multiple comparisons should not be used when assessing evidence about specific hypotheses no adjustment for multiple comparisons will be performed [85]. To evaluate the magnitude and direction of the intervention effects mediated by intrapersonal, interpersonal and environmental processes, the product-of-coefficient method will be used [86]. A first set of GEE regression models will assess the impact of the intervention condition (regression coefficient α) on the residualized change score of the hypothesized mediators (Table 1), after controlling for significant covariates. A second set of GEE regression models will estimate the independent effects of the intervention condition and residualized changes in the mediators (regression coefficient β) on changes in the outcome variables. The significance of the product of the regression coefficients α and β (representing the mediated effect of the intervention) will be tested using bias-corrected bootstrap methods as outlined by Pituch and colleagues [87].

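### With 20 schools, the planned bias-corrected bootstrap test of mediation exceeds its 5% level when exactly one of the two paths is clearly non-zero

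*Protocol article*

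**What the plan says.** Identifying the factors that mediate the intervention is a named secondary aim (Aims section). The Data analysis section prescribes the product-of-coefficients method. One set of GEE models gives α, the effect of intervention condition on change in the mediator. A second set gives β, the effect of change in the mediator on change in the outcome. The significance of the product αβ "will be tested using bias-corrected bootstrap methods", following a cited source. All analyses are to adjust for clustering by school, and no adjustment for multiple comparisons is made.

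The Sample size calculations section powers mediation on the same test. It aims "to detect a moderate mediated effect size with 0.8 power, using a significance level of 0.05 with a two-tailed test and bias-corrected bootstrap methods", states that "61 independent observations are needed", and assumes "standardized regression coefficients α and β of ~ 0.39". It uses "an average school cluster effect of 0.03 for the mediators", 9% loss and 30 children per school. For the main outcomes it works "With a previously observed school clustering effect of 0.018".

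The article does not say whether schools or children are resampled, or whether the bootstrap is parametric.

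**The concern.** The null hypothesis αβ = 0 holds in three situations: both paths are zero, only α is zero, or only β is zero. A 5% test should reject no more than 5% of the time in each.

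When one path is zero and the other is not, two things push the rejection rate up.

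- **Bias correction.** The sampling distribution of a product of two estimates is skewed. The correction takes the share of bootstrap products below the estimate, converts it to a normal score and moves both interval limits by it. With a skewed product this reads skewness as bias and tends to move the interval away from zero.
- **Few schools.** α is a between-school quantity. A bootstrap of 5 or 10 schools per side understates its variance and makes no allowance for the few degrees of freedom.

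The one-path null is a realistic one here. The section on the theoretical basis says the candidate mediators were chosen because the theory behind them has worked before, and the Mediators section says their measures have predictive validity. β may therefore be non-zero for many of them, and the open question is whether the programme moved them. Factors named as mediators in error could steer the content of later programmes.

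**Working it through.** **The plan's own figures.** The protocol gives no type I error for this test beyond the nominal 0.05. Its mediation sample size is 100 in total. From the stated inputs, 61 × [1 + (30 − 1) × 0.03] / (1 − 0.09) = 61 × 1.87 / 0.91 = 125, so 100 is not reproduced. The accompanying figure of 20 per school does not fit 20 schools either (100/20 = 5). This is a separate matter and does no harm at the planned size: 600 × 0.91 / 1.87 = 292 effective observations, against 61 needed.

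**Inputs to the error-rate check.**

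- From the protocol: 20 schools, 30 children each (about 27 after 9% loss), mediator ICC 0.03, outcome ICC 0.018, two-sided 5%.
- Assumed: equal allocation (5 schools per arm), equal school sizes, and ordinary linear regression in place of GEE on residualized change scores.
- Contrasts: pooling two arms against two gives 10 v 10 schools. Two indicators plus an interaction, coded 0/1, give 5 v 5 simple effects.

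**Simulation.** 1,000 bootstrap resamples per trial and 2,000-5,000 simulated trials per setting. The simulation error near 10% is √(0.1 × 0.9 / 5000) = 0.4 points, or 0.7 points with 2,000 trials. α is the arm difference in mediator SDs, so the protocol's standardized 0.39 is a shift of about 0.39 / 0.5 = 0.78 SD in a balanced contrast. β is the standardized slope. Schools are resampled within arm for the two school-bootstrap columns. Rejection rates (%) under a true null:

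| Contrast | α | β | Bias-corrected, schools | Percentile, schools | Bias-corrected, parametric | Joint test, school t | Monte Carlo product interval, t draws |
|---|---|---|---|---|---|---|---|
| 10 v 10 | 0 | 0 | 1.3 | 0.4 | 0.7 | 0.2 | 0.1 |
| 10 v 10 | 0 | 0.14 | 10.7 | 7.0 | 8.6 | 4.4 | 4.2 |
| 10 v 10 | 0 | 0.39 | 8.7 | 7.9 | 6.6 | 4.6 | 4.7 |
| 10 v 10 | 0.39 | 0 | 10.7 | 7.1 | 7.7 | 5.0 | 4.5 |
| 5 v 5 | 0 | 0.14 | 13.8 | 10.5 | 8.3 | 4.3 | 4.2 |
| 5 v 5 | 0 | 0.39 | 13.9 | 13.1 | 8.2 | 5.9 | 6.0 |
| 5 v 5 | 0.39 | 0 | 11.6 | 7.1 | 5.5 | 3.0 | 2.4 |
| 5 v 5 | 0.14 | 0 | 4.0 | 2.2 | 1.2 | 0.5 | 0.5 |

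Over all settings with one path clearly non-zero, the school-resampled bias-corrected test rejects about 8-11% (10 v 10) and 11-15% (5 v 5). The parametric version rejects about 5.5-9%. With both paths zero, school resampling gives 1.2-2.7%. A small non-zero α (0.14, with β = 0) gives about 4% or less.

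**Splitting the excess.** In the three one-path rows at 10 v 10, bias-corrected minus percentile is 10.7 − 7.0 = 3.7, 8.7 − 7.9 = 0.8 and 10.7 − 7.1 = 3.6 points. The bias correction therefore accounts for about 1-4 points.

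The rest can be checked by hand for the case α = 0 with β large. Resampling k schools per side shrinks the standard error by √((k − 1)/k), so the effective critical value is 1.96 × √((k − 1)/k), to be judged against t with 2(k − 1) degrees of freedom.

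- k = 10: 1.96 × √0.9 = 1.86; P(|t| > 1.86) on 18 df = 7.9%. The simulated percentile rate is 7.9%.
- k = 5: 1.96 × √0.8 = 1.75; P(|t| > 1.75) on 8 df = 11.8%. The simulated percentile rate is 13.1%.

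**Power at the planned effect** (standardized α and β both 0.39): 1.00 for the bias-corrected, percentile and joint tests at 10 v 10; 0.998 for the bias-corrected and 0.987 for the joint test at 5 v 5.

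**The case against.** Several points can be made for the plan.

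- **The bootstrap scheme is not shown.** The article defers to a cited source, and an analysis plan may say more. This stands as a limit on the size: a parametric, cluster-adjusted scheme gives about 5.5-9%, not 11-15%. It does not remove the point, because that range still lies above 5% and the bias-corrected test itself is fixed in the text.
- **The higher figures depend on 5 v 5 contrasts.** The stated comparisons for behavioural outcomes pool two arms against two, which would be 10 v 10. This stands too. The prescribed coding with an interaction term leaves the 5 v 5 reading open, so both are reported.
- **The simulated model is simpler than the planned one.** True: covariate adjustment and unequal school sizes are not represented, so the rates are approximate.
- **The practical harm is modest.** Table 1 has 12 rows. If all 12 had exactly one real path, a 10% rate in place of 5% would add 12 × 0.05 = 0.6 false mediators per outcome and time point, on a secondary aim. This is fair and argues against alarm.

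A reader might infer that inert factors will be named as mediators at two or three times the nominal rate. The documents do not support that. For a factor with neither path, the test rejects well under 5% of the time. At the protocol's own path size (β = 0.39, 10 v 10) the rate is about 8-9%. A reader might also blame the bias correction alone, but much of the excess remains without it. Child-level resampling would give 13-18% when α is zero, but it would contradict the stated adjustment for school clustering and should not be assumed.

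**Conclusion.** The point holds in a limited form. A test stated to run at two-tailed 5% is liberal with 20 schools when exactly one path is clearly non-zero: roughly 8-11% for 10 v 10 contrasts and 11-15% for 5 v 5 under school resampling, and 5.5-9% under a parametric cluster-adjusted scheme. It is conservative when both paths are zero and does not exceed 5% when the only non-zero path is a small α. Both the bias correction and the small number of schools contribute.

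The figures rest on equal allocation, equal school sizes, linear models and the protocol's ICCs. The change is worth making: mediation is a named aim tested without multiplicity adjustment, and at the planned effect the bias correction offers almost no power in return.

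**What to change.** In the Data analysis section, replace the bias-corrected bootstrap as the test of mediation.

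- Declare mediation only when both paths are significant at 5%. Test α against a t reference on between-school degrees of freedom (schools minus arm parameters, 20 − 4 = 16 when all four arms are modelled). Test β with a small-sample-corrected, school-clustered standard error.
- Report αβ with an interval that uses the same between-school degrees of freedom, for example a Monte Carlo product interval with t draws. This had error rates of 0.1-6% in the simulations. Switching only to a plain percentile school bootstrap is not enough: it gives about 5-8.5% at 10 v 10 and 6.5-13% at 5 v 5, and could exclude zero when the joint test does not declare mediation.
- In the Sample size calculations section, base the mediation power statement on the same test.

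This takes a wording change and a few lines of code, with no new data. The real cost is power for mediated effects below the planned moderate size; in one simulated setting of that kind it fell from 0.75 to 0.59. At the planned effect it stays at about 0.99 or more.

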## Discussion

Sedentary behavior and physical activity may have independent detrimental and positive effects (respectively) on children's cardio-metabolic health. Very few interventions have targeted reductions in children's total sitting time in the school and family settings. Even fewer interventions have examined the separate and combined effects of targeting reductions in sedentary behavior and increases in physical activity and only two have used objective measures. This 18-month intervention with 12-month tapered maintenance period is unique in its approach to delivery of school curriculum and homework in less sedentary and more active ways. As the key agents of change in children's health behaviors, involvement of teachers and parents is critical. If shown to be successful and cost-effective this intervention may have implications for educational policy and practice, and ultimately the health of young children in Australia and elsewhere.

## Appendix 1

'Road trip/Stations around the room' standing lesson strategy

### Aim

To complete small group activities related to a specific area of study, by physically moving between stations located around the room.

### Outline

The lesson is planned as a series of activities, placed at stations around the classroom. Children are organised into groups (allocated by the teacher). Groups spend a designated period of time at each station completing the activity, before moving onto the next station. All children must remain standing at each station as activities are designed to be easily performed standing (e.g. through use of high benches or clipboards; by keeping written work relatively minimal; by telling children to take turns at being 'scribe' etc).

Teachers can specify the group structure (number of children, how groups are selected), the number of stations, amount of time spent at each station and the associated activities.

### Examples

- Fill in worksheets

- Leave your group's answer on a pile at the station

*- Keep a journal of all of the activities *(write sentences or draw pictures)

- Write responses on large sheets of paper/whiteboards

### Suggestions for stations

**• English**: One chapter/event from a story at each station including comprehension questions.

**• L.O.T.E**.: Match up word-cards and picture-cards; sentences on large posters or interactive whiteboards with blank spaces for children to fill with the correct word (offer lists of choices).

Culturally relevant creative activities, such as origami.

**• Maths: **Set of addition, multiplication or simple division problems - one series per station.

Spatial tasks - fitting shapes into defined spaces (puzzles).

Problem-solving activities +/- problems- Example: "You have a bucket with 150 mL of water, a 40 mL jar and a 50 mL jar. How will you use these to measure out 30 mL of water into this pot?" (If possible, supply the water and jars at the station, so the children can physically do the task).

Fractions tasks - each station based around a different theme- Example: different ways to express '1/2' (50%, 0.5, 2/4, 3/6). Include props, such as blocks or coloured paper cut into a number of fractions.

**•Humanities**: Historical events. These could be read-and-comprehend tasks- Example: "In which year did Captain Cook discover Australia? Describe his landing."

**•Creative task**: "Imagine you are living in Antarctica, draw some of the clothes you would need to wear to keep warm."

### Options

•At the end of the lesson, the children can come together and the teacher can lead a discussion of their work; or groups can exchange work for correction.

### Equipment/preparation required

✓Activities for each station (copies/laminated cards of reading passages, math problems, props for problem-solving activities etc)

✓Pens/pencils and paper/workbooks (for children to record answers at each station)

✓ *(optional) *One clipboard per group/per child

✓ *(optional) *Worksheets for each station (if these are to be completed)

## Appendix 2

'Road trip/Stations around the room' standing lesson strategy

### Aims

To practice spelling or simple number patterns verbally while standing and passing a bean-bag.

### Outline

The children are asked to stand and the teacher nominates a number series or a set of words, relevant to the current lesson. The teacher gives a bean-bag to one student, who states the first number in the pattern or letter in the word. That child then throws the bean-bag to another child, who says the next number/letter then passes the bean-bag on, and so on.

All children remain standing throughout the game, but once a child has passed the bean-bag, they must change their posture/position to signify that they have had their turn.

**Table T3:** Teachers can specify

Subject of game (examples):	The actions performed by children before/after their turns (examples):
• *Spell "..." (word from the current spelling list or story being read)* • *Multiples of... (during a maths lesson)* • *Count up to 100 by twos/fives*	• *Everyone stand up, when you've had your turn, stand on one leg* • *Everyone stand up, after your turn stand on one leg/bend down and touch your toes* • *Everyone stand with their arms out to the sides, after your turn, place hands on head* • *Everyone jog on the spot, after you've had your turn, start hopping*

### Equipment/preparation required

✓Bean-bag (provided) or newspaper balls to throw

*✓ (optional) *Spelling-list on the board
